**Laboratory measurements**

Residual free chlorine concentration will be measured from the samples of stored household water once a week and on unannounced visits by using the residual chlorine test kit(Wagetech 225 comparator colour disc**) .**Water samples will be collected from randomly selected 50% of the households water storage containers from both the intervention and control groups at the baseline and end of the study. The samples will be collected with sterile technique in 150 ml sterile plastic vessels containing sodium thiosulfate to neutralise any free chlorine in the water samples. Environmental health science graduates will collect samples and transport with icepacks to the Haramaya University bacteriology laboratory for processing within six hours of collection for analysis**.** Most probable number (MPN) will be used for the analysis of the sample and MPN table to quantify Escherichia coli which are regarded as the most reliable indicator of fecal contamination (wright 2004)

**Statistical analysis**

All the data will be double entered into EPI info. Intention- to- treat analysis will be applied to compare between the intervention and control groups. Mean will be calculated to determine the proportion of households who use the intervention. Generalized Estimation Equation (GEE) will be used to compare the prevalence and incidence of diarrhea between the intervention and control arms while T-test will be used to compare the mean weight gain between the two groups.

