**Enrolment and randomization**

We will use cluster level randomization to avoid ethical concerns and minimize the potential transfer of the intervention between the two groups. Ethiopian population census enumeration area map will be used to identify the clusters. There are 64 clusters (enumeration area) in study site. We will randomly select 36 clusters to participate in the study. Cluster selection will be done by central statistics authority using simple random sampling. Households in the selected clusters with at least one child under the age of five year will be identified by census. This is because we are expecting higher prevalence and incidence of diarrhea and the effect of the intervention would be higher among this group. Twenty four children will be selected randomly from the each cluster for follow up. Assigning of the clusters in to the intervention and control group will done by independent person using random sampling technique. Field workers will approach selected households in each cluster for baseline survey.

64 clusters

Randomly selected

36 cluster

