**Randomization**

**Intervention Control**

18 clusters, 432 children

18 clusters, 432 children

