**Follow up Follow up**

6921 person week observation

Intention to treat analysis

6921 person week observation

Intention to treat analysis

**An**

**Baseline survey:** we will collect basic information including demographic and socioeconomic information, water sources and water handling practices, access and water quality, housing conditions, and pre-intervention diarrhea rates.

**Interventions:** The intervention for this study will be 1.25% Sodium hypochlorite solution locally branded as “watergauard”. The intervention household will receive the hypochlorite disinfectant for household water treatment while the control groups will continue their usual practice. Both the intervention and control households use Jerricans for water collection and storage. Local women will be selected for the distribution of the intervention (sodium hypochlorite). They will be trained on how to use sodium hypochlorite for household water treatment and explain to the intervention households how to treat water. The intervention will be distributed for 16 weeks.

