**Outcomes:**

Primary outcome for this study is the occurrence of diarrhea among under-five children. Diarrhoea is defined as three or more loose or watery stools in 24 hours. Diarrhea is considered as new episode if it occurred after a period of three diarrhea free days (Morris 1994, Wright 2006). Incidence will be calculated as the number of new episodes divided by the total number of person–weeks observation and longitudinal prevalence as the number of weeks of diarrhea divided by the total number of weeks of observation for each child ( Morris 1996, Schmidt 2011) .

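### The primary GEE is not tied to the enumeration area, the unit randomised; a child-level GEE, which the text permits, would have a type I error of about 26% at the protocol's own design effect

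*Protocol*

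**What the plan says.** - **Unit randomised.** Protocol, Enrolment and randomization: "We will use cluster level randomization to avoid ethical concerns and minimize the potential transfer of the intervention between the two groups". The clusters are census areas: "There are 64 clusters (enumeration area) in study site", and "We will randomly select 36 clusters to participate in the study". The flow chart gives each arm "18 clusters, 432 children".
- **Children and records.** "Twenty four children will be selected randomly from the each cluster for follow up". The Diarrhoea monitoring section has field workers record diarrhoea every week, and follow-up lasts 16 weeks. The data are therefore weeks within children within areas.
- **Sample size.** The Sample size section uses a cluster-trial method with a design effect of three.
- **Analysis.** Protocol, Statistical analysis: "Generalized Estimation Equation (GEE) will be used to compare the prevalence and incidence of diarrhea between the intervention and control arms". No cluster unit, working correlation, variance estimator or covariate is named. The same sentence gives weight gain a t-test and does not mention clustering.
- **Outcome definition.** In the Outcomes section, longitudinal prevalence has as its denominator "the total number of weeks of observation for each child". Incidence is defined on total person-weeks.
- **Baseline.** The Baseline survey paragraph lists "housing conditions, and pre-intervention diarrhea rates" among the items collected. No use of them in the analysis is stated.

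**The concern.** A GEE is not defined until its cluster is named. These data have two candidates: the child, who contributes up to 16 weekly records, and the enumeration area, which was randomised. Only the area gives a standard error that reflects the randomisation. A child-level GEE allows for correlation between weeks in one child but treats children in the same area as independent. The design effect of three shows that the investigators themselves expect strong correlation between those children.

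Naming GEE therefore does not settle that the area is handled. The unqualified t-test for weight gain adds to the doubt, because nothing in the Statistical analysis section carries the randomised unit forward from the design. The validity of the primary p-value and confidence interval is at stake.

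A smaller issue remains even with the area as cluster. The ordinary sandwich variance is biased downwards with 18 areas per arm, and normal critical values are slightly too small.

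**Working it through.** **1. Inputs.** From the protocol: 36 areas, 18 per arm, 24 children per area, 16 weekly records, 11% incidence, 10% dropout, design effect 3. Assumed: two-sided 5% test, 11% read as a weekly rate (the protocol gives no time unit), between-child coefficient of variation (CV) 0.8, between-area CV 0 to 0.5, and a design effect expressed relative to independent children.

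**2. The protocol's own figures.** 18 × 24 = 432 children per arm, as stated. A design effect of 3 with 24 children per area means 1 + 23 × ICC = 3, so ICC = 2/23 = 0.087. The 18 areas per arm do not follow from the stated inputs: about 2,167 children per arm are needed if 11% is a proportion, and about 149 if it is a weekly rate. That is a separate question and nothing below depends on it.

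**3. GEE clustered on the child, by formula.** Ignoring a design effect D leaves the standard error too small by a factor √D, so the true error is 2[1 − Φ(1.96/√D)].
- D = 1.5: 11.0%
- D = 2: 16.6%
- D = 3: 1.96/√3 = 1.132, giving 25.8%

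**4. GEE clustered on the area, by formula.** With normal critical values in place of t on 34 df (36 areas minus two parameters), the error is 2·P(t34 > 1.96) = 5.8%. Adding the downward bias of the uncorrected sandwich, roughly 17/18 in variance, gives 2·P(t34 > 1.96 × √(17/18)) = 6.5%.

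**5. Simulation under no effect.** Log-Poisson GEE with independence working correlation, gamma variation between areas and between children, 10% dropout, 6,000 trials per row. Rejection rates in %:

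| Area CV | Simulated design effect | Child, z | Area, z | Area, 18/17 correction, t34 | Area, Mancl–DeRouen, t34 |
|---|---|---|---|---|---|
| 0 | 0.94 | 5.2 | 6.8 | 5.3 | 4.8 |
| 0.15 | 1.32 | 10.2 | 6.8 | 5.0 | 4.4 |
| 0.25 | 1.93 | 17.8 | 7.0 | 5.5 | 4.9 |
| 0.30 | 2.30 | 21.4 | 6.8 | 5.6 | 4.8 |
| 0.40 | 3.17 | 29.1 | 6.9 | 5.2 | 4.7 |
| 0.50 | 4.08 | 36.2 | 7.2 | 5.5 | 4.8 |

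The Monte Carlo standard error near 5% is √(0.05 × 0.95/6,000) = 0.3 points. A further simulation with 20,000 trials per setting, at area CV 0.15, 0.25 and 0.35, gave 10.2%, 17.6% and 26.3% for the child-level GEE. It gave 6.7% to 6.8% for the area-level GEE with z, and 5.1% to 5.2% for the corrected version with t on 34 df.

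**6. Baseline adjustment.** If an area's baseline and follow-up rates correlate at ρ, adjustment multiplies the variance of the comparison by 1 − ρ². The protocol gives no ρ, so these values are assumptions:

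| ρ | Variance reduction | Power, starting from 80% |
|---|---|---|
| 0.1 | 1% | 80.4% |
| 0.3 | 9% | 83.6% |
| 0.5 | 25% | 89.9% |

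**The case against.** The strongest reply is that silence is not error. GEE is a method for correlated data. The trial randomises areas and is sized with a cluster-trial method, so its authors plainly knew about clustering. Nothing states that the GEE will be clustered on the child. The per-child wording in Outcomes defines a measure and does not name the GEE subject. If longitudinal prevalence is one summary per child, only a level above the child gives the GEE anything to cluster on. Variance corrections and covariate lists are commonly left to a statistical analysis plan, which may exist.

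Much of this stands. A reader might infer that the primary analysis has an error rate above 5%. The document does not support that, because the rate depends on choices it does not make, and with area clusters and a correction it is about nominal.

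A reader might also infer that the plan fits treatment arm alone and discards baseline, so that chance imbalance biases the result. The protocol is only silent on covariates. Leaving out baseline does not bias a randomised comparison or inflate type I error, since a valid area-level standard error already covers chance imbalance. Nor can adjustment for age be said to be available: the Baseline survey paragraph mentions demographic information only in general terms.

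The reply does not remove the missing cluster unit. Weekly records per child make the child-level reading a real one, and the unit of analysis in a cluster trial is a design statement that the protocol should make.

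**Conclusion.** The point holds as a conditional one. The protocol names GEE for the primary comparison without tying it to the randomised enumeration area.

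- If the GEE is clustered on the child, the type I error is about 26% at the protocol's own design effect of three, some five times nominal. In simulation it is about 10% to 26% for assumed area CVs of 0.15 to 0.35.
- If it is clustered on the area with an ordinary sandwich and normal critical values, the error is about 6.5% to 7%, an excess of 1.5 to 2 points.
- If it is clustered on the area with a small-sample correction and a t reference, the error is about 5%.

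The first gap carries the finding. The variance correction and the baseline adjustment complete the specification and are not defects in themselves. The 26% rests on taking the design effect of three as the true ratio of variances; the simulated rates rest on the assumed CVs; the precision gain rests wholly on an assumed correlation.

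**What to change.** In the Statistical analysis section, state that:

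1. the GEE for diarrhoea incidence and prevalence takes the enumeration area as its cluster;
2. the variance is a small-sample corrected sandwich with a t reference, on 34 df unadjusted or 33 df with one area-level covariate;
3. the primary model adjusts for the area's pre-intervention diarrhoea rate, with the unadjusted result given as a sensitivity analysis.

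The simulated error rates in the working are for the unadjusted model. The adjusted one should be checked in the same way before the wording is final.

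**Cost.** Wording only; the baseline rates are already to be collected. Against an uncorrected area-level analysis, the interval is wider by about (2.032/1.96) × √(18/17) = 1.067, or 7%, with the simple correction. The baseline covariate costs one degree of freedom, which is poor value if the correlation is near 0.1 and good value if it is near 0.5.

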**Sample size**

The sample size is calculated using methods published by Hyes and Bennett (Hyes 1999). It is assumed that 11% incidence of diarrhea among children under-five years of age (baseline survey), 80% power, 10% drop out, 95% confidence interval and design effect of three from clustering. We calculated 18 clusters, 24 children under the age of five years per cluster will be followed for 16 weeks to detect 40% reduction in the incidence of diarrhea between the intervention and control groups.

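### The t-test named for weight gain makes no allowance for cluster randomisation, so as naturally read its type I error exceeds 5% for any positive intracluster correlation

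*Protocol*

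**What the plan says.** The Enrolment and randomization section makes the enumeration area the unit of allocation: "We will use cluster level randomization to avoid ethical concerns and minimize the potential transfer of the intervention between the two groups". The flow diagram under Randomization shows "18 clusters, 432 children" in each arm. The Sample size section sets the cluster size ("24 children under the age of five years per cluster will be followed for 16 weeks") and plans for a "design effect of three from clustering".

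The section on anthropometric measurement names weight gain as the secondary outcome. Each child is weighed at baseline and at the end of the study.

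The Statistical analysis section gives the diarrhoea outcomes a GEE. In the same sentence it gives weight gain a different method: "T-test will be used to compare the mean weight gain between the two groups". It does not say whether the observations are children or cluster means. Nothing elsewhere in the protocol adds a cluster term, cluster summary or robust variance for this outcome.

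**The concern.** A two-sample t-test assumes independent observations. Children in one enumeration area share their allocation. They may also share water sources, food supply, season and field team. If their weight gains are correlated for such reasons, 24 children from one area carry less information about the treatment effect than 24 independent children. A child-level t-test ignores this: its standard error is too small, its confidence interval too narrow and its p-value too low.

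Weight gain is the first secondary objective and the only health outcome in the child that is measured by instrument. Diarrhoea is reported by a caregiver in a trial that the protocol says cannot be blinded, and the Background itself warns of responder and observer bias. Readers will therefore look to weight gain as an objective check on the diarrhoea result. A falsely significant weight benefit would seem to support a diarrhoea effect that may itself be biased.

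This is not a detail left for a statistical analysis plan. The protocol names a specific test, and a plan that followed it would carry the problem forward.

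**Working it through.** **Inputs from the protocol**
- Clusters per arm: 18 (Sample size; flow diagram).
- Children per cluster: m = 24 (Sample size).
- Children: 18 × 24 = 432 per arm, which agrees with the flow diagram; 2 × 432 = 864 in all.
- Drop-out: 10% (Sample size: "80% power, 10% drop out"), giving a mean cluster size of 24 × 0.90 = 21.6.
- Significance level: two-sided 5%, taken from the 95% confidence level in the Sample size section.
- Design effect: 3, set for diarrhoea incidence. The implied ICC is (3 − 1)/(24 − 1) = 0.087.

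**Input not in the protocol.** There is no ICC, standard deviation or design effect for weight gain. The ICCs of 0.005 to 0.05 below are assumptions. The standard deviation cancels, so it is not needed.

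**Formulas**
- Design effect: DE = 1 + (m − 1) × ICC.
- Reported SE divided by true SE = 1/√DE.
- True two-sided type I error = 2 × [1 − Φ(1.96/√DE)].

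**Example at ICC 0.02.** DE = 1 + 23 × 0.02 = 1.46. √1.46 = 1.208 and 1.96/1.208 = 1.622. The type I error is 2 × [1 − Φ(1.622)] = 10.5%.

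**Results.** The simulation used 10,000 trials per ICC, with 18 + 18 clusters of 24 children and no treatment effect.

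| ICC | DE (m = 24) | Reported SE / true SE | Type I error, formula | Type I error, simulated | Formula with m = 21.6 |
|---|---|---|---|---|---|
| 0 | 1.00 | 1.00 | 5.0% | 4.7% | 5.0% |
| 0.005 | 1.12 | 0.95 | 6.3% | 6.2% | 6.2% |
| 0.01 | 1.23 | 0.90 | 7.7% | 8.0% | 7.4% |
| 0.02 | 1.46 | 0.83 | 10.5% | 10.2% | 9.9% |
| 0.05 | 2.15 | 0.68 | 18.2% | 17.7% | 17.0% |
| 0.087 | 3.00 | 0.58 | about 26% | 26.5% | 24.2% |

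In the last row, the nominal 95% confidence interval covers the true difference about 74% of the time (100% − 26%). Drop-out at the planned 10% changes little.

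**Check of the remedy.** In the same simulated trials, a t-test on the 36 cluster means (36 − 2 = 34 degrees of freedom) held the type I error between 4.7% and 5.4% at every ICC, including zero.

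**The case against.** Four points can be made on the other side.

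1. **The unit is not stated.** The protocol does not say that the test is run on individual children, and a t-test on cluster means would fit the same words and be valid. This stands as a limit: the child-level test is the natural reading, not the literal text. It is natural because weight is taken child by child, cluster means are mentioned nowhere, and the t-test is set against a GEE. That contrast is only supportive, since the protocol does not state the clustering level of the GEE either. If cluster means were intended, the sentence still has to say so.

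2. **The size is unknown.** A reader might infer that the protocol's own figures put the false-positive rate near 26%, or at least well above 5%. The documents do not support that. The design effect of 3 belongs to a calculation for diarrhoea incidence, and weight change over 16 weeks need not cluster to the same degree. At an ICC of 0.005 to 0.01 the inflation is only to about 6% to 8%. The direction is certain for any positive ICC; the size is not.

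3. **Lack of adjustment is not an error.** A reader might also fault the comparison for leaving out baseline covariates. An unadjusted comparison is valid under randomisation, and the choice of covariates is commonly left to the statistical analysis plan. Baseline weight is collected and already enters through the subtraction. The protocol does not list age or sex among the baseline items and says nothing on how strongly age drives weight gain.

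4. **The outcome is secondary.** This is true. The primary diarrhoea comparison uses GEE and is untouched by this point. That limits the consequence, but it does not make the named test suit the design.

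**Conclusion.** Wrong as written. The trial randomises 36 enumeration areas and allows for clustering in its sample size, yet it fixes a test for weight gain that makes no allowance for clustering. Read naturally, the test has a type I error above 5% for any positive ICC: about 6% at ICC 0.005, 8% at 0.01, 10.5% at 0.02 and 18% at 0.05. It would reach about 26% only if the design effect planned for diarrhoea carried over to weight gain.

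These figures rest on three assumptions: the child-level reading, equal clusters of 24, and ICCs that the protocol does not supply. The conclusion that the method does not match the randomisation needs only the first of these and a positive ICC.

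**What to change.** Replace the t-test wording in the Statistical analysis section with one named method that respects the clusters. Either of these would do:
- a two-sample t-test on the 36 cluster mean weight gains, 18 per arm, with 34 degrees of freedom; or
- a linear mixed model or GEE for weight gain, with enumeration area as the cluster and a small-sample correction.

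These are alternatives, not equivalents. Once drop-out makes cluster sizes unequal they can weight the areas differently and give different estimates, so the protocol should choose one in advance.

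Adjustment for the baseline weight already collected is an optional gain in precision, as is adjustment for age if it is recorded. Neither is needed for validity.

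The change takes one sentence and no new data, visits or children. The cost is a wider confidence interval. Relative to the child-level interval, the standard error grows by √DE: about 1.06 times at ICC 0.005 (√1.115) and 1.73 times at a design effect of 3 (√3). That extra width is the uncertainty which the present test would leave out.

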**Secondary objective:**

1. To determine the effectiveness of household water chlorination in increasing weight gain among under-five children.
2. To determine the acceptability of household water chlorination among the intervention households

**Study design and setting:** A community based randomised field trial will be conducted to determine the acceptability and effectiveness of household water disinfection with chlorine on reducing the prevalence and incidence of diarrhea and weight gain among under-five children in randomly selected clusters of Kersa Demographic and Health Research Centre field site. The study area has a population of 47,036 distributed among the 10 kebeles of which 7870 are children under-five years of age. All the households do not have running water. Families walk to collect water from springs, streams, or wells. The study will be conducted for a 16-weeks period from June to August 2011.

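### Weight gain is assigned a plain t-test between arms although enumeration areas are randomised, so its p-value and confidence interval ignore clustering

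*Protocol*

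**What the plan says.** The first secondary objective in the protocol is "To determine the effectiveness of household water chlorination in increasing weight gain among under-five children". Under Enrolment and randomization the protocol states "We will use cluster level randomization" and "We will randomly select 36 clusters to participate in the study", the clusters being census enumeration areas with 24 children drawn from each. The flow chart gives each arm "18 clusters, 432 children". The Sample size section allows for a "design effect of three from clustering".

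The Statistical analysis section then separates the outcomes. For diarrhoea, "Generalized Estimation Equation (GEE) will be used to compare the prevalence and incidence of diarrhea between the intervention and control arms". For weight, in the second half of the same sentence, "T-test will be used to compare the mean weight gain between the two groups". It states no unit of analysis, cluster-level summary, random effect, robust standard error or design-effect correction for weight gain. The general intention-to-treat statement does not deal with clustering.

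**The concern.** Because areas are randomised, the difference between arms has to be judged against the variation between areas. Children in one area share water, food supply and season, so their weight gains are likely to be correlated. A child-level t-test divides the total variance by the number of children and refers the result to 862 degrees of freedom. The design supplies 34. The protocol recognises clustering in its design, its sample size and its diarrhoea analysis, and then drops it for weight gain.

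Weight gain matters more here than its secondary rank suggests. Diarrhoea is reported by caregivers in a trial that the protocol says cannot be blinded, and its Background stresses responder and observer bias. Weight is the only health outcome that is measured rather than reported. Residual chlorine and *E. coli* are also measured, but they describe the water. A chance difference between two sets of 18 areas could too easily be read as a nutritional benefit or harm, and so as support for the diarrhoea result.

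**Working it through.** **Inputs from the protocol.** 36 areas, 18 per arm, 24 children per area, 10% drop-out, and a design effect of 3 (set for diarrhoea). The head count reproduces: 18 × 24 = 432 per arm and 36 × 24 = 864 in total. The protocol gives no standard deviation, ICC or power for weight gain, so there is no weight-gain figure to reproduce.

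**Assumption.** The ICC for weight gain is taken as 0.01, 0.02 and 0.05. As an upper illustration I add the value implied by a design effect of 3, which is (3 − 1)/(24 − 1) = 2/23 = 0.087.

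**Formulas.** With total variance σ² and m children per area:

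- Variance of an arm mean that the child-level t-test assumes: σ²/432.
- Actual variance: (σ²/432) × DE, where DE = 1 + (m − 1) × ICC.
- True two-sided type I error of the child-level test: 2 × [1 − Φ(1.963/√DE)], where 1.963 is the 97.5% point of t on 862 degrees of freedom. Coverage of its 95% interval is one minus this.
- Correct interval width relative to the child-level one: √DE × 2.032/1.963, where 2.032 is the 97.5% point of t on 34 degrees of freedom.

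**Example.** At ICC 0.02, DE = 1 + 23 × 0.02 = 1.46 and √DE = 1.208. Then 1.963/1.208 = 1.62, giving a type I error of 10.4%.

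| ICC | DE | Type I error | Coverage of 95% interval | Correct width ÷ child-level width | 864/DE |
|---|---|---|---|---|---|
| 0 | 1.00 | 5.0% | 95.0% | – | 864 |
| 0.01 | 1.23 | 7.7% | 92.3% | 1.15 | 702 |
| 0.02 | 1.46 | 10.4% | 89.6% | 1.25 | 592 |
| 0.05 | 2.15 | 18.1% | 81.9% | 1.52 | 402 |
| 0.087 | 3.00 | 25.7% | 74.3% | 1.79 | 288 |

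The last column is the number of independent children that would carry the same information.

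**Drop-out.** With 24 × 0.9 = 21.6 children per area (about 778 with both weights), DE = 1 + 20.6 × ICC. The error then runs from 7.4% at ICC 0.01 to 24.0% at ICC 0.087.

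**Simulation.** In 20,000 null trials at each ICC, with 18 against 18 areas of 24 children, the child-level t-test rejected in 4.8%, 7.7%, 10.9%, 17.9% and 25.7% of trials at ICC 0, 0.01, 0.02, 0.05 and 0.087. A t-test on the area means rejected in 4.8% to 5.1% throughout.

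**The case against.** The strongest reply is that the protocol does not say that the t-test is run on children. A t-test on 18 against 18 area means is also a t-test, and it is valid. The authors cite a sample size method for cluster trials, so they knew about clustering, and a SAP could name the unit of analysis. This stands only in part. The wording does not exclude area means, but the sentence sets the t-test against GEE and speaks of the mean gain in two groups, so a child-level test is the natural reading. Nor is this a detail left open. The protocol names a method, and a SAP that follows it would carry the error forward. If area means were intended, the same sentence is needed to say so.

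A second reply is that the ICC for weight gain is unknown, that at ICC 0 there is no inflation, and that the design effect of 3 belongs to diarrhoea. That is right as to size. The direction holds for any ICC above zero, and even 0.01 raises the error by about half.

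A third is that only a secondary outcome is affected and that the analysis can be corrected from data already collected. Both points are true. They limit the damage and make the correction easy, but they do not make the stated test valid.

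**Conclusion.** The concern holds. As written, the weight-gain comparison does not respect the unit of randomisation, and its p-value and interval will be too optimistic if gains are correlated within areas. Over the assumed ICC range of 0.01 to 0.05 the true type I error is 7.7% to 18.1%. It reaches 25.7% if the diarrhoea design effect of 3 also applied to weight gain, which the protocol does not claim.

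The conclusion rests on the child-level reading of the sentence and on an ICC above zero. The figures also take equal area sizes. The diarrhoea analysis is untouched. The point is separate from adjustment for age and from missing end weights, and would remain if both were settled.

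**What to change.** Replace the t-test clause in the Statistical analysis section with wording such as: *Mean weight gain will be compared between arms with the enumeration area as the unit of inference, by a two-sample t-test on the 18 and 18 area mean gains (34 degrees of freedom). The estimated ICC will be reported with the result.*

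A linear mixed model with a random intercept for enumeration area and small-sample degrees of freedom is a sound alternative. It agrees exactly with the area-mean test only when areas are of equal size, which drop-out may upset. One of the two should therefore be named in advance as the main analysis.

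The cost is one sentence, with no extra children, visits or measurements. The interval will be wider, by a factor of 1.15 to 1.79 over the range above. Only a small part of that comes from the critical value (2.032 against 1.963). The rest is clustering that the design already contains.
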